## Abstract

**Background:**

Retrospective data demonstrates that robotic-assisted thoracoscopic surgery provides many benefits, such as decreased postoperative pain, lower mortality, shorter length of stay, shorter chest tube duration, and reductions in the incidence of common postoperative pulmonary complications, when compared to video-assisted thoracoscopic surgery. Despite the potential benefits of robotic surgery, there are two major barriers against its widespread adoption in thoracic surgery: lack of high-quality prospective data, and the perceived higher cost of it. Therefore, in the face of these barriers, a prospective randomized controlled trial comparing robotic- to video-assisted thoracoscopic surgery is needed. The RAVAL trial is a two-phase, international, multi-centered, blinded, parallel, randomized controlled trial that is comparing robotic- to video-assisted lobectomy for early-stage non-small cell lung cancer that has been enrolling patients since 2016.

**Methods:**

The RAVAL trial will be conducted in two phases: Phase A will enroll 186 early-stage non-small cell lung cancer patients who are candidates for minimally invasive pulmonary lobectomy; while Phase B will continue to recruit until 592 patients are enrolled. After consent, participants will be randomized in a 1:1 ratio to either robotic- or video-assisted lobectomy, and blinded to the type of surgery they are allocated to. Health-related quality of life questionnaires will be administered at baseline, postoperative day 1, weeks 3, 7, 12, months 6, 12, 18, 24, and years 3, 4, 5. The primary objective of the RAVAL trial is to determine the difference in patient-reported health-related quality of life outcomes between the robotic- and video-assisted lobectomy groups at 12 weeks. Secondary objectives include determining the differences in cost-effectiveness, and in the 5-year survival data between the two arms. The results of the primary objective will be reported once Phase A has completed accrual and the 12-month follow-ups are completed. The results of the secondary objectives will be reported once Phase B has completed accrual and the 5-year follow-ups are completed.

**Discussion:**

If successfully completed, the RAVAL Trial will have studied patient-reported outcomes, cost-effectiveness, and survival of robotic- versus video-assisted lobectomy in a prospective, randomized, blinded fashion in an international setting.

**Trial registration:**

ClinicalTrials.gov, NCT02617186. Registered 22-September-2015. https://clinicaltrials.gov/ct2/show/NCT02617186

## Introduction

### Background and rationale

Retrospective data demonstrates that robotic-assisted thoracoscopic surgery (RTS) provides highly precise instrumentation, 3-dimensional visualization, and a less steep learning curve as compared to video-assisted thoracoscopic surgery (VATS) [1], and RTS may also represent oncological benefit by allowing for improved lymph node dissection [2, 3]. Other potential advantages of RTS-Lobectomy over VATS-Lobectomy are decreased postoperative pain, lower mortality, shorter length of stay in hospital, shorter chest tube duration, and reductions in the incidence of common postoperative pulmonary complications [4–6]. Despite the potential benefits of robotic technology, there are two major barriers against its widespread adoption in thoracic surgery.

The first barrier is the lack of high-quality prospective data. To our knowledge, there are no prospective trials comparing VATS-Lobectomy to RTS-Lobectomy for early-stage lung cancer. In the largest multi-institutional series on RTS-Lobectomy with 325 patients, Park and colleagues reported a median length of stay in hospital of 5 days, 25% perioperative morbidity, 0.3% mortality, and 8% rate of conversion to thoracotomy [3]. Although these results compare favorably to most historical series on VATS-Lobectomy, this trial did not have a VATS-Lobectomy control arm. In a recent database analysis using State Independent Databases of 8 states, a propensity-matched cohort of RTS-Lobectomy was compared to VATS-Lobectomy [6]. Robotic resection was associated with reductions in mortality (0.2% vs 1.1%), length of stay in hospital (5.9 days vs 6.3 days), and overall complication rates (43.8% vs 45.3%) when compared with VATS.

The second major barrier to the widespread adoption of robotic technology in thoracic surgery is the perceived higher cost of RTS pulmonary lobectomy. In a recent trial of the Nationwide Inpatient Sample, it was determined that the incremental additional cost of RTS-Lobectomy over VATS-Lobectomy was $4,708 [7]. This dataset was limited by the absence of patient characteristics, the early learning curve for robotic surgeons, the large proportion of robotic cases being performed in community hospitals with small lobectomy volumes, and the lack of follow-up after discharge from hospital. Data on Health-Related Quality of Life (HRQOL) outcomes were most notably omitted from this trial, hampering any useful conclusion on the cost-effectiveness of RTS-Lobectomy.

In the face of these barriers, a randomized controlled trial comparing VATS-Lobectomy to RTS-Lobectomy is needed. Prospective randomization will eliminate the biases of retrospective data and will serve to determine whether there exists any advantages to HRQOL or patient outcomes in favour of RTS-Lobectomy over VATS-Lobectomy. Furthermore, through a prospective cost-utility analysis, this trial will provide the highest quality data to evaluate the true economic impact of robotic technology in thoracic surgery.

RTS-Lobectomy has only been recently introduced in Canada, and the volume of preliminary cases in our group (University of Toronto’s Toronto General Hospital (TGH) and McMaster University’s St. Joseph’s Healthcare Hamilton (SJHH)) is a reflection of this novelty. The first case was performed in May of 2011 at the TGH. In the first Canadian series of RTS for pulmonary resection for lung cancer, which included 167 completed cases performed at TGH and SJHH, analysis showed a median operative time of 270 minutes (233–326), a very low rate of conversion to thoracotomy (12/167, 7.2%) and a median hospital length of stay (LOS) of 4 days (3–6) [8]. To measure the effects of the learning curve, the data was stratified by surgeon and evaluated in temporal tertiles. Total operative time decreased significantly (p<0.001) over the learning curve; tertile 1: 309.0 min, tertile 2: 258.5 min and tertile 3: 236.0 min. Median time spent on the robotic console also decreased significantly (p<0.001) over tertiles– 172.0, 136.0, and 116.0 minutes, respectively [8]. Across tertiles, there were no differences in the median number of lymph node stations harvested (8, 8, 8; p = 0.39), length of stay (4, 4, 4; p = 0.16), or the rate of major intraoperative complications (Clavien-Dindo Class ≥ III; 8, 2, 8, respectively; p = 0.28). There were no mortalities.

The early Canadian experience with robotic lung cancer resection demonstrates excellent results that are comparable to those of experienced centers in operative times, length of stay and conversion rates, with further improvement demonstrated by the learning curve effect (Table 1).

**Table 1 pone.0261767.t001:** Outcome comparison between the first 167 cases of RTS-Lobectomy.

	Tertile 1	Tertile 2	Tertile 3
Operative time (minutes)	309.0	258.5	236.0
Time on robotic console (minutes)	172.0	136.0	116.0
Conversion (no., %)	2 (3.0)	2 (4.3)	7 (14.0)
Nodes harvested (no.)	8	8	8
Length of Stay (days)	4	4	4
Major Intraoperative Complications, Clavien-Dindo Class ≥ III (no.)	8	2	8
Mortality (no.)	0	0	0

VATS-Lobectomy is also a well-established procedure in our group. A recent analysis of our experience with 608 patients over the last 8 years demonstrated excellent rates of morbidity (26%) and 30-day mortality (0%), and a median length of stay in hospital of 4 days. More importantly, it was shown that the rate of lymph node sampling during VATS-Lobectomy performed by our surgeons is comparable to the rate of sampling during open lobectomy (Table 2). This is contrary to studies that question the oncological validity of VATS-Lobectomy because of poor rates of lymphadenectomy [9, 10], and demonstrates that our surgeons have reached an expert level of competency in this operation [3].

**Table 2 pone.0261767.t002:** Rates of lymphadenectomy in VATS-Lobectomy versus Thoracotomy in our group.

Nodal Station	Left Upper		Left Lower		Right Upper and Middle		Right Lower	
	VATS	Open	VATS	Open	VATS	Open	VATS	Open
2R					79%	77%	55%	52%
2L								
4R					95%	91%	73%	79%
4L	52%	64%	73%	74%				
5	64%	53%	50%	30%				
6	17%	6%	8%	11%				
7	73%	70%	97%	93%	94%	99%	90%	90%
8			17%	0%			7%	7%
9			79%	48%			21%	38%
10R					62%	46%	31%	38%
10L	47%	58%	54%	56%				
11R					72%	54%	69%	76%
11L	64%	70%	92%	81%				
12R					93%	79%	83%	93%
12L	87%	83%	54%	89%				

This trial will not include patients undergoing thoracotomy as a third comparator arm for two reasons. First, the superiority of RTS-Lobectomy and VATS-Lobectomy over thoracotomy has been consistently demonstrated in multiple high-quality studies [3–5], thereby eliminating clinical equipoise on this question. Second, in the present era of minimally invasive thoracic surgery, patients who undergo thoracotomy typically present with more advanced disease, and will thereby introduce a selection bias that will be difficult to mitigate.

### Objectives

#### Primary objective

Phase A of this trial is intended to determine the difference in patient-reported HRQOL outcomes between RTS-Lobectomy and VATS-Lobectomy at 12 weeks post-surgery. We hypothesize that for patients with early-stage non-small cell lung cancer (NSCLC), RTS-Lobectomy results in improved patient-reported quality of life as compared to VATS-Lobectomy.

#### Secondary objectives

In Phase A of this trial, we will compare differences in short-term clinical outcomes, and HRQOL outcomes at weeks 3 and 7; and months 6 and 12, which coincide with the intervals of oncological surveillance. We will also compute resource utilization and calculate the incremental cost effectiveness between RTS-Lobectomy and VATS-Lobectomy.

In Phase B of this trial, we will compare the difference in the 5-year survival data between the two arms. We will also compare differences in HRQOL outcomes at months 18 and 24; and years 3, 4, and 5, which coincide with the intervals of oncological surveillance. We will also compute resource utilization and calculate the incremental cost effectiveness between RTS-Lobectomy and VATS-Lobectomy.

RTS-Lobectomy is a new technology that has not been studied extensively yet against VATS-Lobectomy, so equipoise still exists. However, based on preliminary data from our experience and from literature, we hypothesize that for short-term clinical outcomes, RTS-Lobectomy leads to higher quality pathological staging by improved lymphadenectomy, and is associated with shorter duration of chest tube drainage; shorter hospital length of stay; less intraoperative blood loss; lower postoperative analgesia requirements; and less chronic postsurgical pain as compared to those who receive VATS-Lobectomy.

### Trial design

The trial is an international, multi-centered, blinded, randomized controlled trial. Patients will be randomized to RTS-Lobectomy versus VATS-Lobectomy at a 1:1 allocation ratio (Fig 1).

**Fig 1 pone.0261767.g001:**
[figure not shown]
CONSORT diagram of trial design.

## Methods: Participants, interventions and outcomes

### Study setting

In Canada, participants will be recruited from two academic hospitals: McMaster University’s St. Joseph’s Healthcare Hamilton (SJHH) in Hamilton, Ontario and the University of Toronto’s Toronto General Hospital (TGH) in Toronto, Ontario. In Canada, these two hospitals have the highest volume for robotic thoracic surgery. Participants will also be recruited from two international academic hospitals: University of Florida’s UF Health Shands Hospital in Gainesville, Florida, USA, and Rouen Normandy University’s CHU-Hôpitaux de Rouen in Rouen, France.

### Eligibility criteria

#### Participants

Participants are eligible to participate in the trial if they sign the Patient Information and Informed Consent Form (PICF) and meet the following eligibility criteria:

*Inclusion criteria*:

Age ≥ 18 yearsClinical stage I, II or IIIa non-small cell lung cancer (NSCLC)Candidates for minimally invasive pulmonary lobectomy, as determined by the operating surgeon.

*Exclusion criteria*:

Patients who received neoadjuvant treatmentClinical stage IIIb or IV NSCLCNot a candidate for minimally invasive lobectomy

During the COVID-19 pandemic, participants will be eligible to participate in the trial if they meet the eligibility criteria and provide either written or verbal consent.

#### Surgeons

The trial may be subject to performance bias, based on surgeon preference. To mitigate this, only surgeons who have demonstrated proficiency by independent completion of more than 30 VATS- and 30 RTS-Lobectomies [11] will be able to recruit participants for the trial.

### Who will take informed consent?

The investigator will introduce the trial at the time of consent for the operation. Under the guidance of the investigator, the trial coordinator will inform the potential trial participant of all pertinent aspects of the trial. Potential trial participants will be informed that their medical care will not be affected should they choose not to participate. The trial coordinator will encourage and answer any and all questions. Prior to participation in the trial, the trial participant, trial coordinator, and the investigator will print their name, sign, and date two copies of the PICF–one for the participant and one for the study team.

During the COVID-19 pandemic, the trial coordinator will inform the potential participant of all pertinent aspects of the trial by phone. Prior to participation in the trial, the PICF will be discussed over the phone. If the potential participant has an email address and access to a printer and scanner, then the PICF will be emailed to the potential participant for him or her to print, sign, scan, and email back. If the potential participant does not have an email address, nor access to a printer and scanner, then verbal consent will be recorded if provided. The consent discussion information will be recorded on the Consent Discussion Form.

### Additional consent provisions for collection and use of participant data and biological specimens

This is not applicable as the participant data collected will only be used for this trial. Biological specimens are not collected for this trial.

## Interventions

### Explanation for the choice of comparators

Both RTS-Lobectomy and VATS-Lobectomy are minimally invasive, standard of care surgeries. Despite the many potential benefits of RTS-Lobectomy, there are a couple of major barriers against its widespread adoption in thoracic surgery: lack of high-quality prospective data, and the perceived higher cost of RTS-Lobectomy. To the best of our knowledge, there is no prospective randomized controlled trial comparing these two types of minimally invasive surgeries, nor is there any useful conclusion on the cost-effectiveness of RTS-Lobectomy, and so we intend to compare RTS-Lobectomy and VATS-Lobectomy in this prospective, randomized controlled trial to overcome these barriers.

### Intervention description

The surgical procedure in both the intervention arms will involve pulmonary lobectomy and mediastinal lymph node sampling of stations 10R, 11R, 4R, 7, 8, 9 for right sided resections, and stations 10L, 11L, 4L, 5, 6, 7, 8, 9 for left sided resections. Each participant’s surgery will be videotaped.

In addition, participants in the:

*VATS-Lobectomy Arm*:

will undergo the procedure through a 4-port technique with or without an accessory incision and,

*RTS-Lobectomy Arm*:

will undergo the procedure according to the CPRL-4 technique (using 3 or 4 arms) as described by Cerfolio [12].

### Criteria for discontinuing or modifying allocated interventions

During the surgical procedure, if it is determined by the surgeon that in order to complete the surgery safely and successfully, the participant needs to be converted from their allocated intervention to a thoracotomy, then the allocated surgery will be discontinued. The participants will remain in their allocation group for purposes of intention-to-treat analysis.

### Strategies to improve adherence to interventions

The participants who enroll into this trial would be, as determined by the operating surgeon, candidates for minimally invasive pulmonary lobectomy. Hence, the participants should be able to undergo the surgery they were allocated to. However, above all else, the participants’ safety comes first, and if need be, then the surgeon will discontinue the allocated surgery for the participants’ safety.

Also, each participant’s surgery will be videotaped with a camera in the operating room. Any identifying features of the participant, including their face, will not be videotaped. There will be no audio on the videotapes. Videotapes will be reviewed by a member of the Video Review Committee for quality assurance purposes.

### Relevant concomitant care permitted or prohibited during the trial

As this trial is intended to determine the difference in outcomes between RTS-Lobectomy and VATS-Lobectomy, any concomitant care that is relevant and/or necessary during the participants’ standard of care during the trial will be permitted.

### Provisions for post-trial care

There are no trial-related provisions for ancillary or post-trial care. If a participant is injured or harmed directly from participating in the trial, all necessary medical treatments will be made available to them at no cost. Financial compensation for such things as lost wages, disability, or discomfort due to this type of injury or harm is not routinely available.

### Outcomes

#### Primary outcome

The primary outcome is difference in HRQOL scores between the treatment groups, as measured by the EQ-5D-5L questionnaire at week 12.

#### Secondary outcomes

To determine:

Short-term clinical outcome differences, the following will be collected: clinical staging, pathological staging, number of lymph nodes sampled, admission date, date of surgery, discharge date, chest tube removal date, intraoperative blood loss, post-operative analgesia, and post-surgical pain.Resource utilization, a healthcare resource utilization tracking system will be developed for the specific purpose of the trial in order to allow for an accurate cost analysis. Variables that will be tracked include utilization of operating room time, operating room staff, surgical instruments and consumables, admission to critical care beds, hospital length of stay, duration of intravenous analgesia, postoperative complications, and costs associated with chronic post-surgical pain up to one year after surgery.Cost-Effectiveness, the incremental cost per quality-adjusted life year (QALY) gained will be calculated.Differences in HRQOL scores between the treatment groups, the EQ-5D-5L questionnaire will be administered at weeks 3 and 7; months 6, 12, 18, 24; and years 3, 4, and 5, which coincide with the intervals of oncological surveillance.Overall survival, the difference in 5-year survival rate between the two groups will be calculated.

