#### Baseline data collection

Baseline data including demographics (e.g., age, BMI, gender), medical history (e.g., smoking, alcohol use, comorbidities, analgesia consumption, pain, previous thoracic surgery, previous cancer), tumour characteristics (e.g., clinical stage, histology), and physiology (e.g., pulmonary function) will be collected. In addition, participants will be asked to complete the Trial Health Questionnaire and they will be provided with a Study Diary.

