#### Trial health questionnaire

The Trial Health Questionnaire includes questions on the participant’s employment status, social activities (e.g., smoking, alcohol use), pain assessment (Numeric Pain Rating Scale) and two surveys, the EQ-5D-5L [16] and the Reintegration to Normal Living Index (RNLI) [17].

The NPRS is a numeric version of the visual analog scale, with 0 representing no pain and 10 representing the worst pain the participants can imagine. Participants will be asked to indicate their pain on movement (deep breathing or mobilization). The EQ-5D-5L has been validated for a number of chronic conditions, including cardiovascular and respiratory disease. The EQ-5D-5L is comprised of a descriptive system as well as a visual analog scale that assesses dimensions related to mobility, self-care, usual activities, pain/discomfort, and anxiety/depression. Respondents are asked to report their health states by rating each dimension as one of five levels (no problems, slight problems, moderate problems, severe problems and extreme problems). The RNLI is a self-report questionnaire used to evaluate global function status of a patient during rehabilitation which was developed to qualitatively assess the ability of individuals with traumatic or incapacitating illnesses to reintegrate into normal life. The RNLI is a questionnaire that is comprised of 11 questions that assesses mobility, self-care, daily activity, recreational activity, and family roles. Reintegration to normal living was defined as the reorganization of physical, psychological, and social characteristics of an individual into a harmonious whole so that one can resume well-adjusted living after incapacitating illness or trauma [18]. Each domain contains a visual analogue scale. On one end: “does not describe my situation” (1 or minimal integration) and “fully describes my situation” (10 or complete integration). Individual item scores are summed to provide the total score. The higher the score, the better the patients perceived integration.

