**SECONDARY**			
Short-Term Clinical Outcomes			
*Pathological Staging*	Improved	Pathological stage	McNemar’s test
*Lymph nodes*	More	Number of lymph nodes harvested	Independent t-test, Wilcoxon rank sum test/linear regression
*Duration of chest tube drainage*	Shorter	Number of days between surgery and chest tube removal	Kaplan-Meier method, Cox regression
*Hospital length of stay*	Shorter	Number of days between admission and discharge	Kaplan-Meier method, Cox regression
*Intra-operative blood loss*	Less	Volume of Intra-operative blood loss (mL)	Independent t-test/Wilcoxon rank sum test/ linear regression
*Post-operative analgesia requirements*	Less	In-hospital consumption (days, type, amount)	Independent t-test/Wilcoxon rank sum test/linear regression
*Chronic post-surgical pain*	Less	In-hospital pain (daily, scale)	Independent t-test/Wilcoxon rank sum test/ANOVA
Patient-reported Health-Related Quality of Life (HRQOL) outcomes	Improved	HRQOL scores, measured by the EQ-5D-5L at 3 and 7 weeks, and 6 and 18 months, and 1,2, 3, 4 and 5 years	Examine the distributions/ regression/ANOVA
Resource Utilization and Cost Effectiveness	More	Resource utilization tracking system, EQ-5D-5L, Return to Normal Living Index (RNLI), and employment status at 12 months	Incremental cost per quality-adjusted life year (QALY) gained will be calculated
Overall Survival	Improved	5-year survival difference	Kaplan-Meier method and cox proportional hazard models. Survival curves will be compared using the Log-rank test

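### Table 3 plans no baseline-adjusted analysis of daily in-hospital pain, although the same pain score is collected before surgery, so the comparison is valid but less precise than it could be.

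*Protocol article*

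**What the plan says.** All references are to the protocol article.

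- **Outcome.** The Secondary outcomes section lists "intraoperative blood loss, post-operative analgesia, and post-surgical pain" among the short-term data. The Secondary objectives hypothesise lower analgesia needs and less pain after robotic surgery, and the Secondary analysis section measures both in hospital.
- **Baseline data.** Baseline data collection covers "medical history (e.g., smoking, alcohol use, comorbidities, analgesia consumption, pain, previous thoracic surgery, previous cancer". It adds that "participants will be asked to complete the Trial Health Questionnaire and they will be provided with a Study Diary". That questionnaire contains a "pain assessment (Numeric Pain Rating Scale) and two surveys", and for the pain item "Participants will be asked to indicate their pain on movement (deep breathing or mobilization".
- **In-hospital data.** Hospital stay data collection uses the same scale, also on movement, every day from postoperative day 1 to discharge. Analgesic consumption is recorded daily over the same period.
- **Analysis of pain.** The Table 3 row labelled chronic post-surgical pain defines the outcome as the daily in-hospital score and gives the method as "Independent t-test/Wilcoxon rank sum test/ANOVA".
- **Analysis of analgesia.** The row above it, with outcome "In-hospital consumption (days, type, amount", lists the t-test, the Wilcoxon test and linear regression.
- **General text.** Statistical methods for primary and secondary outcomes plans unadjusted tests, multivariable linear regression for adjusted analyses of continuous outcomes, and ANOVA for repeated measures. It names no covariates.
- **Randomisation.** Sequence generation stratifies by surgeon.

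**The concern.** Three continuous short-term outcomes in Table 3 have linear regression among their methods: lymph nodes, blood loss and analgesia. Lymph nodes and blood loss have no pre-operative value of the same measure. In-hospital pain has one, on the same scale and under the same condition, yet its row lists no regression. The row also does not match the general text, which plans adjusted regression for continuous outcomes without excepting pain.

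What is at stake is precision. Part of the spread in post-operative pain scores may come from differences between patients that were present before surgery. A model with the baseline score removes that part from the error; a t-test, a Wilcoxon test or a plain ANOVA on post-operative scores leaves it in. No power is stated for pain, so precision that costs nothing is worth taking. An analysis plan that followed the Table 3 row as written would carry the omission forward.

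**Working it through.** **1. The plan's own figure.** The only Phase A sample size is for EQ-5D-5L at 12 weeks: difference 0.07, SD 0.16, 80% power, level 0.05 (two-sided assumed).

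- n per arm = 2 × (1.960 + 0.842)² × 0.16² / 0.07² = 2 × 7.849 × 5.224 = 82.01, rounded up to 83. Total 166, as stated.
- With 10% drop-out: 83 / 0.9 = 92.2, rounded up to 93 per arm. Total 186, as stated.

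The figure reproduces, but it says nothing about power for pain. It serves here only to give 93 per arm, the Phase A recruitment target; the Secondary objectives place the short-term outcomes in Phase A.

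**2. Unadjusted comparison of a pain score.** In SD units, the difference detectable with 80% power is 2.802 × √(2/93) = 2.802 × 0.147 = 0.411.

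**3. Adjusted for baseline.** With correlation r between baseline and in-hospital score, the residual variance is multiplied by 1 − r². Then:

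- detectable difference = 0.411 × √(1 − r²)
- power at the 0.411 SD effect = Φ(2.802 / √(1 − r²) − 1.960)
- equivalent unadjusted size per arm = 93 / (1 − r²)

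The article gives no r, so a range is assumed:

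| r (assumed) | Variance reduction | Detectable difference (SD) | Power at 0.411 SD | Equivalent n per arm |
|---|---|---|---|---|
| 0 (unadjusted) | 0% | 0.411 | 80.0% | 93 |
| 0.1 | 1% | 0.409 | 80.4% | 93.9 |
| 0.2 | 4% | 0.403 | 81.6% | 96.9 |
| 0.3 | 9% | 0.392 | 83.6% | 102.2 |
| 0.4 | 16% | 0.377 | 86.4% | 110.7 |
| 0.5 | 25% | 0.356 | 89.9% | 124.0 |

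**4. Chance imbalance.** The SD of a chance difference in mean baseline pain is √(2/93) = 0.147 baseline SDs. An imbalance of that size moves the unadjusted estimate by r × 0.147 outcome SDs: 0.015 at r = 0.1 and 0.073 at r = 0.5. The unadjusted standard error already allows for this variation, so it is part of the same loss of precision and not a second harm.

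**5. Limits.** The table describes one score per patient analysed by ANCOVA. It does not give the gain for a mixed model of several daily scores, which also depends on the correlation between days.

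**The case against.** The strongest reply is that the general text already covers pain. It plans adjusted linear regression for continuous outcomes and does not exclude pain, and its sentence on repeated measures explains the ANOVA entry. On this view a summary table merely omits a method given elsewhere. Covariate lists normally belong in the statistical analysis plan, which is not shown. This stands in part. Unnamed covariates are no finding in themselves. But for pain the table names specific methods, and none is described as using the baseline score. The row and the general text need reconciling whatever the analysis plan says.

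A second reply is that the gain may be small. All patients receive patient-controlled analgesia managed by a pain service (Hospital stay section), which could weaken the link between pre-operative and in-hospital pain. That is fair: at a correlation of 0.1 to 0.2, power moves only from 80% to between 80.4% and 81.6%.

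A third is timing. Enrollment and baseline lists the questionnaire after randomisation. Participants are to be blinded and the baseline score precedes surgery, so it remains usable as a covariate.

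Two stronger readings are tempting and are not supported. A reader might infer that analgesic use, too, is compared only with unadjusted tests. Its Table 3 row lists linear regression, and nothing in the article ranks the methods separated by slashes. A reader might also infer that chance imbalance in pre-operative pain biases or invalidates the result. In a 1:1 randomised comparison the unadjusted test keeps its error rate.

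**Conclusion.** The point holds for in-hospital pain, as a loss of precision. Table 3 gives no baseline-adjusted model for an outcome whose same-scale baseline value is collected, and it is out of step with the general statistical methods. For an effect detectable with 80% power at 93 per arm, adjustment raises power to between 80.4% (correlation 0.1) and about 90% (correlation 0.5). The gain is negligible at the low end and worth having from about 0.4 upwards. This rests on an assumed correlation, a single score per patient and a two-sided 0.05 level.

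For analgesic consumption only a smaller suggestion remains: use the pre-operative value in the regression already listed. The primary outcome, the sample size and the type I error are not affected.

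**What to change.** - **Pain row of Table 3.** Make the main analysis a linear mixed model of the daily in-hospital NPRS scores, or ANCOVA on the score of one day fixed in advance, with baseline NPRS on movement and surgeon as covariates. Keep the unadjusted tests as supportive. The mixed model also suits patients who contribute different numbers of days; the group's own robotic series reports a median stay of 4 days (3–6).
- **Analgesia row.** Include pre-operative analgesic use and surgeon as covariates in the linear regression already listed.

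The cost is two lines in Table 3 or the statistical analysis plan. The baseline values and the surgeon stratum are already recorded, so no new data or patients are needed.
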